### Data collection and follow-up

All information required according to the protocol will be entered in the paper-based case report forms. The data will be collected as and when they are obtained and recorded in these case report forms. Data entry will be performed on electronic media. Each missing data item will be coded. Clinical research assistants will carry out regular follow-up visits at the study sites. The approach to missing data will be aggressive, and the investigators will attempt to recover/retrieve any missing data by contacting all the patients or their next-of-kin in case of discharge from the hospital. In case of withdrawal of consent, the data of the patient will not be analysed. Data of each patient will be anonymised and use the initials of the patient and the unique code assigned to him or her. All serious adverse reactions (e.g. angioedema) will be brought to the notice of the ethics committees of the respective institutions, as well as the Data Safety and Monitoring Board (DSMB).

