## Methods

### Study design

Continuing vs withholding ACEIs/ARBs is a multi-centric, open-label, randomised controlled two-arm trial, with a 1:1 allocation of hypertensive patients undergoing major non-cardiac surgery to either continue or stop their ACEIs/ARBs. When admitted to the hospital, patients will be randomised to either continue their ACEIs/ARBs including on the day of surgery (group A) or discontinue the drugs 24–36 h before surgery (group B). The primary endpoint will be a composite outcome of all-cause 30-day mortality, major adverse cardiovascular events (acute myocardial infarction, stroke, arrhythmias requiring intervention, hypertensive crises, acute pulmonary oedema, postoperative cardiogenic shock), acute kidney injury, postoperative respiratory failure, sepsis and unplanned ICU admissions. The Standard Protocol Items: Recommendations for Interventional Trials (SPIRIT) checklist is provided in Additional file 2, and the schedule of the participant enrolment in the study (SPIRIT figure) is shown in Fig. 1.

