### Ethical aspects

The study was approved by the Institutional Ethics Committee of AIIMS Bhubaneswar (1 June 2020 vide letter no. T/EMF/Anesth/20/10) and by the ethics committee of each of the collaborating hospitals. Furthermore, the study was registered in the Clinical Trials Registry of India (CTRI/2021/01/030199, registered on 4 January 2021). Patients will receive written information regarding the trial, the possible risks and benefits, and an informed consent will be obtained from them by the research assistants before enrolling them into the trial.

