### Randomisation and blinding

All study patients will receive the same standards of care and management, including treatment of any harm resulting from the trial. However, they will receive no compensation as a result of participation in the study. They will be randomised to either continue with their ACEI/ARB treatment (including on the day of surgery) (group A) or to withhold it 24–36 h before surgery (group B) (two doses of the ACEI or ARB will be omitted to account for variation in the timing of administration, i.e. morning or evening). The patient’s blood pressure will be monitored periodically and treated with calcium channel blockers if necessary. Other antihypertensives that the patient may be concurrently receiving will be continued on the day of surgery. All such orders will also be recorded. Following surgery, anti-hypertensive medications including ACEIs/ARBs will be restarted at the earliest and the date of restarting anti-hypertensive therapy will be noted.

Randomisation will be carried out using permuted block randomisation (blocks of 20). The randomisation codes and sequence will be computer-generated by a statistician at each institute. The randomisation codes and the sequence will be kept secure at each participating centre. One code from a block sequence will be allotted each time when the patient is enrolled into the study. Allocation concealment will be with opaque sealed envelopes which will be opened 2 days before surgery. The diagnosis of outcomes will be made by clinicians treating the patients. The data for primary and secondary outcomes will be collected from the anaesthesia and surgical case records by the investigators and the project staff. The project staff will be trained by the investigators in the aspects of data collection and approach to missing data.

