### Statistical analysis

To adjust for confounders, a multivariate logistic regression analysis will be carried out, stratifying for ASA physical status, age, gender, general vs neuraxial anaesthesia and types of surgery. Data will be also stratified according to the centre. Attempts to account for missing data will be made, but since this will be an intention to treat analysis, all data that will be available from each patient will be included in the study.

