### Sample size calculation

Based on an incidence of 25% of the primary endpoint in the reference group [11], a total of 2016 patients will allow an 80% power to detect a 21% relative decrease of complications in the experimental group. To account for dropouts, a total of 2100 patients (700 at each centre) will be included. The analysis will be an intention-to-treat analysis. Since one interim analysis will be planned after recruiting 1000 patients according to the O’Brien and Fleming method, the interim alpha will be set at 0.0052 and the final nominal alpha at 0.048 (Additional file 1). The *P* values and respective sample sizes were based on a final sample size of 2100, and 1 interim analysis at halfway point was calculated using the “gsDesign” package of the R statistical software v4.0.0 (R Statistical Corp, Vienna, Austria).

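### Leaving patients who withdraw consent out of the analysis contradicts the stated intention-to-treat analysis and, in an open-label trial, allows exclusions that depend on arm and outcome

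*Protocol article*

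**What the plan says.** Three statements in the protocol article define who is analysed.

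- Data collection and follow-up: "In case of withdrawal of consent, the data of the patient will not be analysed". It does not separate data recorded before withdrawal from data that would have come later, or withdrawal before allocation from withdrawal after it.
- Sample size calculation: "The analysis will be an intention-to-treat analysis".
- Statistical analysis: "since this will be an intention to treat analysis, all data that will be available from each patient will be included in the study".

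Three further statements bear on when a patient can withdraw and what the patient knows by then.

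- Study design describes a "multi-centric, open-label, randomised controlled two-arm trial, with a 1:1 allocation".
- Ethical aspects: "an informed consent will be obtained from them by the research assistants before enrolling them into the trial".
- Randomisation and blinding: "Allocation concealment will be with opaque sealed envelopes which will be opened 2 days before surgery".

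No section reconciles the withdrawal rule with the other two statements, and none cites a legal or ethical duty to discard data already collected.

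**The concern.** Intention to treat means that patients are compared as randomised. A rule that drops some of them after the envelope is opened departs from this, and it also discards observations that the Statistical analysis section says will be used.

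The design gives the departure a way to matter. Consent comes first, the allocation is then revealed, and follow-up runs to the 30-day telephone call. A patient can therefore withdraw knowing the arm, or after a complication. The arms also differ in what patients experience before surgery: the article itself plans to study rebound hypertension and case cancellation after withholding. If patients at higher risk withdraw more often from one arm, their removal makes that arm look better. Blinded adjudication does not protect against this, because the events of an excluded patient never enter the comparison. The promised effort to retrieve missing data concerns missing items, not withdrawn consent.

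**Working it through.** **The texts side by side.** Data recorded before a patient withdraws are data held on a randomised patient. The Statistical analysis section includes them; the Data collection and follow-up section excludes them. Both cannot be followed.

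**The plan's own figures.** The article assumes a 25% event rate in the reference group ("Based on an incidence of 25% of the primary endpoint in the reference group"), a 21% relative reduction, 80% power, a final two-stage alpha of 0.048, 2016 patients, and 2100 after allowing for dropout.

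- Planned difference: 0.25 × 0.21 = 0.0525, that is 25% against 19.75%, or 5.25 points.
- Sample size for two proportions (two-sided, 1:1, pooled variance, alpha 0.048): 1001 per arm, 2002 in total, within 1% of 2016. With 1008 per arm the power is 80.3%. The figure reproduces.
- Dropout allowance: (2100 − 2016)/2100 = 84/2100 = 4.0%.

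**Illustration of the effect of exclusion.** The article gives no withdrawal rate, no split by arm and no event risk for withdrawers. The following are assumptions: no true effect, true event rate 25% in both arms, 1050 patients per arm, and overall withdrawal equal to the 4% allowance. If a proportion w of an arm withdraws and these patients have event risk q, the rate among those left is

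(0.25 − w × q) / (1 − w).

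| w | q = 0.40 | q = 0.50 |
|---|---|---|
| 2% | 0.242/0.98 = 24.69% | 0.240/0.98 = 24.49% |
| 3% | 0.238/0.97 = 24.54% | 0.235/0.97 = 24.23% |
| 5% | 0.230/0.95 = 24.21% | 0.225/0.95 = 23.68% |
| 6% | 0.226/0.94 = 24.04% | 0.220/0.94 = 23.40% |

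If q = 0.25, the formula returns 25% for every w: withdrawers at average risk cause no bias, even in unequal numbers. If w and q are the same in both arms, the two rates fall together and the difference stays at zero.

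Spurious difference, A minus B, in percentage points:

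| Withdrawal, A vs B | q = 40–50% in both arms | q = 40–50% in B only (A's withdrawers at 25%) |
|---|---|---|
| 2% vs 6% | 24.69 − 24.04 = 0.65 to 24.49 − 23.40 = 1.09 | 25 − 24.04 = 0.96 to 25 − 23.40 = 1.60 |
| 3% vs 5% | 24.54 − 24.21 = 0.33 to 24.23 − 23.68 = 0.54 (unrounded rates) | 25 − 24.21 = 0.79 to 25 − 23.68 = 1.32 |

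For 2% versus 6%, the share of the planned 5.25 points is 12–21% (0.65/5.25 to 1.09/5.25) if the raised risk applies in both arms, and 18–30% (0.96/5.25 to 1.60/5.25) if it applies in B only.

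**Effect on the type I error, one case.** Take 21 withdrawals in A and 63 in B, q = 0.50 in both. Expected events left are 262.5 − 10.5 = 252 of 1029 in A and 262.5 − 31.5 = 231 of 987 in B. The difference is 0.0109, its standard error about 0.0190, and the ratio about 0.57. With a critical value of 1.977 (alpha 0.048), the chance of rejecting is Φ(0.57 − 1.977) + Φ(−0.57 − 1.977) ≈ 8.5%, against a nominal 4.8%.

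The sign is not fixed. Swapping the arms, or giving withdrawers a risk below 25%, reverses it.

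**The case against.** The strongest reply is that the conflict is one of definition. A site could hold that data whose use a patient has revoked are no longer available, so that the Statistical analysis section never promised to include them. Whether withdrawing consent covers data already recorded depends on the consent form, which is not shown. Part of this stands: a patient's explicit refusal of data use has to be respected, and the fix allows for it. But the rule as stated applies to every withdrawal, including that of a patient who only wants to stop the allocated strategy or the follow-up.

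It can also be said that few patients may withdraw. The strategy is brief, most outcomes come from case records, and later contact is one telephone call. That is fair. Nothing in the article points to a high withdrawal rate. The 84 patients are an allowance for dropouts of any kind, and treating all of them as consent withdrawals is an assumption.

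A reader might infer more than the article supports:

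- That recorded events are erased and the bias could never be examined. The article says only that the data are not analysed. They are entered on case report forms as they arise, and nothing prevents counting withdrawals by arm.
- That the result is an analysis of completers. Only patients who withdraw consent are excluded. Those lost to follow-up or not following their allocation are not, and retrieval of missing data is promised.
- That a spurious difference of 1.0–1.6 points is the expected size. That range needs raised risk among withdrawers in group B alone, which nothing in the article supports over raised risk in both arms.
- That a patient who withdraws before surgery shows recorded postoperative events being lost. Such a patient has none yet; what is lost is the randomised patient and any preoperative observations.

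**Conclusion.** The withdrawal rule is wrong as written. It contradicts two explicit statements in the same article, and it is a stated rule, not detail left to an analysis plan. The contradiction rests on the text alone and needs no assumption.

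The possible bias does rest on assumptions. The design permits exclusions that depend on arm and outcome; it does not show that they will occur. In the illustrations the spurious difference runs from about 0.3 points (3% versus 5%, 40% risk in both arms) to 1.6 points (2% versus 6%, 50% risk in B only), against a planned 5.25. Under no true effect it is zero if withdrawers carry average risk, or if withdrawals match in number and risk across arms. The planned sample size, power and alphas are not in question here.

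**What to change.** Replace the sentence under Data collection and follow-up with: *Patients who withdraw remain in the analysis in their randomised arm using data collected up to withdrawal, unless the patient explicitly revokes use of those data; withdrawals and revocations are reported by arm.*

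In the consent form, separate three decisions: stopping the allocated strategy, stopping follow-up, and withdrawing consent to the use of data.

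This does not supply outcomes that would have occurred after withdrawal. How these are handled (imputation, best-case and worst-case checks) can be left to the analysis plan.

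The cost is one sentence and one consent clause. The article gives the trial as not yet recruiting, and its Protocol amendments section sets out the route through the ethics committees and the registry. The change is easiest before the first patient consents under the current wording. No larger sample is needed: if all 2100 patients are analysed, power is 81.9% at alpha 0.048, against 80.3% with 2016.

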### Clinical data

Baseline data such as age, gender, height, weight, BMI, ASA physical status, surgery, co-morbidities and anti-hypertensive medications will be collected. In-hospital mortality/mortality within 30 days of surgery, postoperative major adverse cardiovascular events (acute myocardial infarction, stroke, acute pulmonary oedema, postoperative cardiogenic shock, acute severe hypertension crisis, severe cardiac arrhythmia requiring therapeutic intervention), the incidence of intra- and postoperative (24 h) hypotension (systolic blood pressure < 90 mmHg), acute kidney injury (based on the serum creatinine item of the KDIGO criteria [9]; baseline serum creatinine will be the preoperative value), hyperkalaemia (serum potassium level > 5.5 meq/L requiring intervention), angioneurotic oedema, sepsis (suspected or culture-positive), postoperative respiratory failure and unplanned ICU admissions will be recorded.

The impact of withholding of ACEIs/ARBs on rebound pre-induction hypertension (blood pressure > 160/90 mmHg) on the day of surgery and case cancellation will also be evaluated. Intraoperatively, the episodes of hypotension will be treated with vasopressors (ephedrine, phenylephrine, norepinephrine and epinephrine). The choice of vasopressor will be left at the discretion of the anaesthesiologist. The lowest arterial pressure, duration of hypotension and total doses of vasopressors (bolus and infusion) will also be collected and reported. Other secondary outcomes noted will be myocardial injury (elevation of serum troponin-t evaluated till 12/24 h after surgery), duration of primary hospital stay and duration of ICU stay. The ancillary and post-trial care of the participants will be as per the standard of care for all patients admitted to the hospital for routine non-cardiac surgery, till their duration of stay in the hospital.

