## Objectives

The primary objective of this study is to evaluate the effect of continuing vs withholding of ACEIs/ARBs on the composite all-cause mortality, major adverse cardiovascular outcomes (acute myocardial infarction, stroke, arrhythmias requiring intervention, hypertensive crises, acute pulmonary oedema, postoperative cardiogenic shock), acute kidney injury, postoperative respiratory failure, sepsis and unplanned ICU admissions in hypertensive patients undergoing major non-cardiac surgery. The secondary objective will be to evaluate the incidence of intraoperative hypotension, myocardial injury, angioneurotic oedema, case cancellations and duration of ICU and hospital stay.

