### Efficacy end-points

The composite primary outcome and the secondary outcomes will be collected for each patient. Diagnosis of complications will be made by the treating physicians. A data adjudication committee will review the appropriateness of the collected data for each outcome measure. Members of the committee will be blinded to the group allocation and comprise non-participating clinicians from each centre.

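### Hyperkalaemia is counted only if a potassium above 5.5 also requires intervention, a decision made by unblinded clinicians, although the protocol uses the threshold alone for exclusion

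*Protocol article*

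**What the plan says.** All places are in the protocol article.

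- **Outcome item (Clinical data).** Among the items to be recorded is "hyperkalaemia (serum potassium level > 5.5 meq/L requiring intervention". Two conditions must hold: a laboratory value and a need for treatment.
- **Eligibility (Exclusion criteria).** Patients are excluded for hyperkalaemia at the preoperative visit on a serum potassium above 5.5 mmol/L, with no treatment condition. For potassium, meq/L and mmol/L are the same number, so the threshold is identical.
- **Blinding (Study design).** "Continuing vs withholding ACEIs/ARBs is a multi-centric, open-label, randomised controlled two-arm trial".
- **Who decides (Randomisation and blinding; Efficacy end-points).** "The diagnosis of outcomes will be made by clinicians treating the patients", and again, "Diagnosis of complications will be made by the treating physicians".
- **Safeguards (same two sections).** "All study patients will receive the same standards of care and management, including treatment of any harm resulting from the trial". Also, "A data adjudication committee will review the appropriateness of the collected data for each outcome measure"; its members are blinded to allocation.
- **Status of the item.** Hyperkalaemia is not in the primary composite (Objectives; Study design). Nor is it among the named secondary items: "The secondary objective will be to evaluate the incidence of intraoperative hypotension, myocardial injury, angioneurotic oedema, case cancellations", followed by the lengths of ICU and hospital stay.

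**The concern.** The article gives no rule for when a raised potassium must be treated, so the second half of the definition is left to the clinician at the bedside, who can know whether the patient continued or stopped the drug. Two patients with the same potassium can therefore be a case and a non-case, and the deciding factor is a judgement that allocation may influence.

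At stake is how far the hyperkalaemia counts by arm can be interpreted. If clinicians in one arm act on a given value more readily than in the other, the comparison partly measures their behaviour and not potassium. This is a safety item, and nothing in the primary analysis depends on it.

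**Working it through.** **1. The definitions side by side**

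| Item | Measured threshold | Treatment condition |
|---|---|---|
| Hyperkalaemia, exclusion criterion | > 5.5 mmol/L | none |
| Hyperkalaemia, recorded outcome | > 5.5 meq/L | yes |
| Hypotension, recorded outcome | systolic < 90 mmHg | none |
| Acute kidney injury, recorded outcome | KDIGO creatinine criterion | none |
| Arrhythmia, recorded outcome | none stated | yes |

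The arrhythmia item, "severe cardiac arrhythmia requiring therapeutic intervention", also carries a treatment qualifier, but it states no measurement that could stand without it. Hyperkalaemia does. The exclusion and outcome definitions do not contradict each other, since they serve different purposes. The exclusion criterion shows only that the value alone was acceptable as a definition elsewhere in the same protocol.

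**2. What the safeguards reach**

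The blinded committee reviews collected data. It can confirm that a value and a treatment were recorded, but it cannot reverse an unblinded decision to treat or not to treat. An untreated value above 5.5 is not a case under the definition, so nothing ensures that it reaches the committee. The promise of equal standards of care is general and sets no potassium treatment rule.

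**3. Possible size**

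The article gives no hyperkalaemia rate, so there is no figure of its own to reproduce. Inputs:

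- n = 2100 / 2 = 1050 per arm (total from Sample size calculation, 1:1 allocation from Study design).
- True rate r of potassium > 5.5, the same in both arms: 1%, 2% or 4% (assumed).
- Share s of those values judged to require intervention, by arm (assumed).

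Formulas: recorded rate in an arm = r × s; recorded ratio = s₁ / s₂; recorded difference d = r(s₁ − s₂). The chance of two-sided p < 0.05 is Φ(d/SE − 1.96) + Φ(−d/SE − 1.96), where SE is the standard error of the difference between the two recorded proportions.

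| Shares | r | Expected events per arm | Ratio | Difference (points) | Chance of p < 0.05 |
|---|---|---|---|---|---|
| 65% vs 65% | any | equal | 1.00 | 0 | 5% |
| 70% vs 65% | 1% | 7.35 vs 6.83 | 1.08 | 0.05 | 5.2% |
| 70% vs 65% | 2% | 14.7 vs 13.65 | 1.08 | 0.10 | 5.5% |
| 70% vs 65% | 4% | 29.4 vs 27.3 | 1.08 | 0.20 | 5.9% |
| 70% vs 60% | 1% | 7.35 vs 6.3 | 1.17 | 0.10 | 5.9% |
| 70% vs 60% | 2% | 14.7 vs 12.6 | 1.17 | 0.20 | 6.9% |
| 70% vs 60% | 4% | 29.4 vs 25.2 | 1.17 | 0.40 | 8.9% |

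Worked example, 70% vs 60% at r = 4%: recorded rates are 2.8% and 2.4%, d = 0.4 points, SE = √(0.028 × 0.972/1050 + 0.024 × 0.976/1050) = 0.694 points and d/SE = 0.576, so the chance is 8.9%.

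Reversing the gaps gives ratios of 65/70 = 0.93 and 60/70 = 0.86; the direction is not known.

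With so few events the normal approximation is rough. Exact binomial enumeration of the pooled z-test gives 5.4%, 7.0% and 8.8% for 70% vs 60%. Under equal shares of 65% its size is 4.5%, 5.2% and 5.0%.

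**The case against.** The strongest reply is that nothing here is an error. An eligibility cut-off and an event definition need not match, and a threshold plus a need for treatment is a recognisable severity-based definition. No differential treatment is shown, and the article offers no mechanism or direction for it. Group B omits only two doses and the drugs are restarted as early as possible after surgery, which narrows the contrast. The error rates above belong to a test that the protocol never announces for this item. Unblinded judgement also affects items that matter more, including components of the primary composite such as arrhythmia, suspected sepsis and unplanned ICU admission. Finally, the article describes no potassium testing schedule, so unblinded clinicians may also decide who is tested, and counting every raised value would not cure that.

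Most of this stands. There is no contradiction between the two definitions, bias is possible but not demonstrated, and the item is peripheral. The testing problem would remain after the change. What does not stand is the inference that the definition should therefore be left alone. The treatment condition adds an avoidable unblinded step where a measured criterion is already written down. Recording treatment as a flag keeps the severity-based count, so no clinical information is lost.

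**Conclusion.** The concern holds, as a minor point to consider. The recorded definition of hyperkalaemia depends partly on an unblinded treatment decision, when the same threshold without that decision is used in the exclusion criteria. Blinded review and the promise of equal care reduce the exposure but do not remove it.

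The size is probably small. There is no bias if the share of raised values treated is equal in both arms. A gap of 5 to 10 percentage points in that share would move the recorded ratio by about 8% to 17% in one direction, or 7% to 14% in the other, and the false-positive chance to at most about 9% in the scenarios examined. Every rate and share is an assumption. The primary result, the alpha and the sample size are untouched.

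**What to change.** Define the event as any serum potassium above 5.5 mmol/L after randomisation within a stated window. Record whether each such value was treated as a separate flag. Report both counts by randomised arm, together with the number of patients tested in each arm. The present definition can still be reported from the flag. Differences in who is tested become visible, although they are not removed.

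The cost is one reworded item and one extra flag, filled from the case records that project staff already abstract, with slightly more abstraction work. Mild elevations will be included: if 65% of values above 5.5 are judged to need treatment (assumed), the extra cases across both arms are 2100 × r × 0.35, which is about 7, 15 or 29 at r = 1%, 2% or 4%. The Trial status section gives the trial as not yet recruiting, so on this document the change can be made before any data exist. Untreated values that are never abstracted would be harder to recover later.

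### Two primary-composite components, sepsis and unplanned ICU admission, rest on the judgement of clinicians who can know the allocation, and blinded review limits this only in part

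*Protocol article*

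**What the plan says.** Study design describes a "multi-centric, open-label, randomised controlled two-arm trial, with a 1:1 allocation of hypertensive patients". The primary composite there includes, besides death and cardiovascular events, "acute kidney injury, postoperative respiratory failure, sepsis and unplanned ICU admissions".

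The Clinical data section says how components are recorded: "sepsis (suspected or culture-positive), postoperative respiratory failure and unplanned ICU admissions will be recorded". The same section ties another component to a laboratory standard: "acute kidney injury (based on the serum creatinine item of the KDIGO criteria".

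On ascertainment, Randomisation and blinding states "The diagnosis of outcomes will be made by clinicians treating the patients", and Efficacy end-points repeats it: "Diagnosis of complications will be made by the treating physicians". The outcome data are "collected from the anaesthesia and surgical case records by the investigators and the project staff". Under Participants, the project staff also check compliance with the allocated group, so they know it.

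Efficacy end-points then adds a safeguard: "A data adjudication committee will review the appropriateness of the collected data for each outcome measure". Its members are blinded, non-participating clinicians.

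**The concern.** Any component makes a patient a primary event, so suspected sepsis or an ICU transfer counts the same as death. As printed, suspicion is enough for sepsis, and no criterion separates a well-supported suspicion from a weak one. An unplanned ICU admission is a decision, taken here by a team that can know whether the drug was continued.

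Two problems can follow. If knowledge of allocation changes how readily sepsis is suspected or a patient is transferred, the arms can differ with no true effect. If many such events have nothing to do with ACEI/ARB exposure, they dilute a true effect and cost power. In either case the credibility of the primary result would depend on its softest components.

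**Working it through.** **Is this a stated definition or only a condensed one?** In the same section the article gives thresholds for acute kidney injury (KDIGO creatinine), hypotension (systolic below 90 mmHg) and hyperkalaemia (above 5.5 meq/L). It also gives words for sepsis, and those words admit suspicion. The looseness is therefore in the printed text and is not a detail left to another document.

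**What can the committee do?** Its material is what treating clinicians diagnosed and staff extracted.
- Suspected sepsis: it can judge whether the record supports the call, but the printed definition is already met by suspicion and no ground for rejection is given.
- ICU admission: it can confirm that the admission happened and was unplanned. It cannot remove the influence of known allocation on the decision.
- Events never suspected, tested for or recorded may not reach it.

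**The plan's own figure.** Inputs from Sample size calculation: 25% in the reference group, 21% relative decrease, 80% power, 2016 patients (1008 per arm), final nominal alpha 0.048. Sidedness is not stated; two-sided is assumed, because one-sided variants give only 1558 to 1658 patients in total.
- p1 = 0.25; p2 = 0.25 × 0.79 = 0.1975; target difference 5.25 points.
- Two-proportion normal approximation without continuity correction: 1001 per arm, 2002 in total, within 0.7% of 2016. The stated size reproduces.
- Rejection probability = Φ((d − z·s0)/s1) + Φ((−d − z·s0)/s1), where d = pA − pB, s0 = √(2·p̄(1−p̄)/n), s1 = √(pA(1−pA)/n + pB(1−pB)/n), z = 1.977, n = 1008.
- At 0.25 vs 0.1975: s0 = 0.01856, s1 = 0.01853, power 80.3%.
- With both arms at 25%, an observed difference of about 1.977 × √(2 × 0.25 × 0.75/1008) = 3.8 points is significant.

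The documents give no component rates, so every input below is an assumption.

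**Differential ascertainment, no true effect**

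| Assumed shift in one arm | Patients (× 1008) | Share of 5.25 points | False-positive rate |
|---|---|---|---|
| none | 0 | 0% | 4.8% |
| 1 point | about 10 | 19% | 7.8% (26% vs 25%) to 7.9% (25% vs 24%) |
| 2 points | about 20 | 38% | 17.1% (27% vs 25%) to 17.8% (25% vs 23%) |

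**Non-differential events unrelated to treatment.** Let f be the proportion of patients in each arm who qualify only through such events.

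| Case | f | Rates | RR | Power |
|---|---|---|---|---|
| Added to the 25%: 0.25 + f vs 0.1975 + f | 3% | 28.0% vs 22.75% | 0.81 | 76.8% |
| | 5% | 30.0% vs 24.75% | 0.83 | 74.8% |
| Within the 25%: 0.25 vs (0.25 − f) × 0.79 + f | 3% | 25.0% vs 20.38% | 0.82 | 69.1% |
| | 5% | 25.0% vs 20.80% | 0.83 | 60.5% |

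**The case against.** The strongest reply is that the safeguard is real. The committee is blinded, its members do not take part in the trial, and its remit covers every outcome measure and the appropriateness of the data. It may well reject weakly supported sepsis calls, and its working criteria may stand in a full protocol or charter that is not shown. That stands. It rules out saying that blinded review can do nothing, and the lack of a charter in the article is not a fault. It does not change the printed definition, and it does not reach the ICU decision.

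A reader might infer that bias would favour withholding, because that is the stated hypothesis and hypotensive patients who continued the drug might be sent to ICU. The documents do not support a net direction. Study hypothesis and Clinical data also anticipate rebound hypertension after withholding, which could prompt admissions in the other arm. An ICU admission caused by real hypotension is an effect of treatment, not an ascertainment error.

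A reader might also infer that a positive culture without organ dysfunction is certainly an event. The parenthesis can equally be read as separating unconfirmed from microbiologically confirmed sepsis. The phrase is ambiguous and names no criterion; no more than that can be said.

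Finally, including care-level events in a composite is a legitimate pragmatic choice, and mortality and creatinine-based kidney injury are less exposed.

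**Conclusion.** The point holds as a weakness in how two primary components are defined and ascertained. No stated figure is wrong and the sample size reproduces. The documents do not show that bias will occur, which way it would run or how large it would be, and the trial is not invalid because of it.

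The calculations show only that the design is sensitive. Against a target difference of 5.25 points, about 10 to 20 patients classified differently in one arm move the false-positive rate to about 8% or 17-18%. Unrelated events in 3-5% of patients cost roughly 4 to 6 points of power if they add to the 25%, or 11 to 20 points if they are part of it. These results rest on the assumed shifts, a two-sided final test at 0.048 and the planned 1008 per arm. The change is worth making now because Trial status says recruitment has not begun.

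**What to change.** 1. In Clinical data, replace the present sepsis wording with a standard objective definition (infection plus new organ dysfunction), applied by the existing blinded committee from data in the case records.
2. In Efficacy end-points, state that the committee's classification is the event that is analysed.
3. Keep unplanned ICU admission in the composite, and record the reason for each one on the case report form.
4. Prespecify a supportive repeat of the primary comparison that drops sepsis based on suspicion only and patients whose sole event is an ICU admission. Report it beside the primary result, not as a second success criterion.

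Cost: an amendment by the route the protocol already describes and a few added case report form fields. The fields must cover whatever organ-function data the chosen sepsis definition needs, since Clinical data does not list a full set. The event rate may fall, so the 25% in Sample size calculation should be rechecked against the stricter definition. Some dependence on what unblinded clinicians test for and record will remain.
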